### Recruitment

#### Identification and invitation

Personal identification numbers of persons diagnosed with cancer at age 0–18 years whose treatment was completed 3 months to 5 years earlier are identified via the Swedish Childhood Cancer Registry (National Quality Registry, initiated in 1982). Their parents, with addresses, are subsequently identified via the Swedish Tax Agency’s Population Registry using their online secure file transfer system (e-transport), and the transfers are managed by Uppsala University IT Services.

We will randomise parents identified via the Swedish Tax Agency’s Population Registry to recruitment blocks of approximately 100 parents using computer-generated simple randomisation, with one recruitment block of parents invited per week until the sample size of 60 participants is reached or a recruitment period of 3 months has passed. To minimise the risk of inviting a parent of a person who has died since receiving data from the Swedish Childhood Cancer Registry, we will request up-to-date information concerning their living status from the Swedish Tax Agency’s Population Registry via Uppsala University IT Services on the same day as sending invitation packs to their parent via post.

We will send invitation packs via post including an invitation postcard, an invitation letter, a participant information sheet, two copies of the consent form (one copy can be kept) and a freepost return envelope. Invitation letters are personalised with the parent’s name, as evidence suggests personalisation can improve recruitment rates.^75^ Those who wish to participate provide consent by returning the consent form in the freepost return envelope. Potential participants who want more information can contact the research team via telephone or SMS.

#### Reminders for those who have not consented within three weeks

If an invited potential participant has not consented within 3 weeks of sending the invitation, we will attempt to identify their telephone number online via internet search engines providing public access to Swedish citizens’ telephone numbers. If a telephone number is identified, we will send an SMS informing that we will make up to three attempts to reach them via telephone over the next 2 weeks. The number of reminder attempts is informed by ENGAGE findings, where a mean of 3.6 recruitment reminder calls were made to reach potential participants.^30^ If we cannot identify a person’s telephone number, we will send a reminder via post together with the invitation pack. Before either reminder type, we will receive up-to-date information concerning the living status of the person treated for cancer during childhood from the Swedish Tax Agency’s Population Registry via Uppsala University IT Services on the same day as sending the reminder to their parent. Those who do not consent by the time recruitment closes (ie, the sample size of 60 participants is reached or a recruitment period of 3 months has passed) are classified as lost to recruitment.

#### Recruitment timeline

We commenced recruitment in June 2026 and will recruit for a maximum of 3 months. Based on enrolment rates observed in the ENGAGE feasibility study and weekly invitation blocks of approximately 100 parents, we anticipate reaching a sufficient number of potentially eligible parents after sending approximately 6–7 blocks. Assuming a 9% randomisation rate, this would yield approximately 54–63 participants, sufficient to achieve the target sample of 60 participants, equivalent to approximately 20 participants per month over the 3-month recruitment period.

#### Consent

Those who wish to participate provide consent by signing the consent form and returning it to the research team using the freepost return envelope. Potential participants provide their telephone number and preferred times and days to be contacted by the research team when returning the consent form. A personal copy of the consent form can be retained.

### Randomisation: intervention or control group

After assessing eligibility during a structured inclusion interview via telephone (see Data collection methods), eligible participants complete the baseline assessment and are thereafter randomly allocated to the intervention or control group in a 1:1 ratio using block randomisation with a block size of 6. The randomisation sequence is computer-generated to ensure unpredictability and conducted through an online software application (https://www.sealedenvelope.com/) by an individual external to the research team. Following randomisation, the individual external to the research team will notify the research team of the participant’s allocation, after which a research team member will inform the participant of their allocation via SMS. For those allocated to the intervention group, a research team member will provide: (1) workbooks (via post together with an introduction note), (2) access to audio files and video case vignettes (online platform link via SMS), and (3) information about their assigned parent guide (via SMS). The research team will notify the assigned parent guide that they have been allocated a participant and the parent guide will contact the participant within 1 week to introduce themselves and schedule the initial assessment session.

### Blinding

Due to the nature of the intervention, participants and parent guides cannot be blinded to group allocation. We will not blind research team members who conduct data collection at post-treatment (12 weeks) and follow-up (6 months post-treatment) assessments. This decision is made because (1) this is a pilot RCT examining feasibility not designed to make inferential statements about potential between-group outcome differences, and (2) the primary outcomes are feasibility outcomes (eg, completion rates and missing data) which are objective and not subject to assessment bias. Blinded outcome assessment was considered but judged impractical given the small size of the research team, who combine trial coordination with data collection. To mitigate potential assessor bias, research team members collecting outcome data will follow a standardised, structured telephone assessment script to collect data, and all collected data are independently double-entered with discrepancies identified and resolved (see Data recording and entry). In a future superiority RCT, research team members conducting outcome assessments will be blinded to group allocation.

### Data collection methods

We will collect data during pre-enrolment, enrolment, and post-randomisation (see table 3).

#### Sociodemographic and medical data

##### Pre-enrolment: identification and invitation via registries

We will first request information from the Swedish Childhood Cancer Registry about persons treated for cancer during childhood: personal identification number to identify the person’s parents in the Swedish Tax Agency’s Population Registry; diagnostic information (age at diagnosis, date of diagnosis, diagnostic group (CSN tumours, leukaemias, lymphomas, solid tumours) and predisposing previous cancer); and treatment dates (end date of primary treatment, end date of relapse treatment and end date of latest treatment).

We will thereafter request information from the Swedish Tax Agency’s Population Registry. For persons treated for cancer during childhood: personal identification number; reason for deregistration from the registry including date of deregistration; mother’s personal identification number; father’s personal identification number; and guardian’s personal identification number, with date of custody. For parents: personal identification number; reason for deregistration from the registry including date of deregistration; name; public registration address; special mailing address; place of birth, place of birth abroad (if relevant); and country of birth.

##### Enrolment: inclusion interview and baseline assessments

On receiving a potential participant’s written consent, we will book, via SMS, a time for the inclusion interview. If the first SMS is not answered, we will send up to two reminders via SMS within 1 week. If these are not answered, we will make up to two attempts to contact the potential participant via telephone the following week. The number of reminder attempts is informed by ENGAGE procedures, where participants were reminded up to five times (telephone, SMS, e-mail) to complete assessments.^30^ Ahead of a booked time, we will send a confirmation and a reminder via SMS 7 days and two working days (if applicable), respectively, before a booked time.

We will assess eligibility during a structured inclusion interview via telephone. If a potential participant fulfils inclusion criteria, they are asked structured questions about their sociodemographic characteristics and medical data for the person treated for cancer during childhood (≈15 min). We will collect the following sociodemographic characteristics for study participants: date of birth, gender identity, relationship and cohabitation status, education level, number and age of children and health problems among other children, housing situation, country of birth and their parents’ country/countries of birth, native language, and previous psychological treatment. We will collect the following sociodemographic characteristics and medical data about the person treated for cancer during childhood: date of birth, gender identity, cancer diagnosis/es, time since first diagnosis, time since end of last treatment, type of cancer treatment/s, and cancer recurrence (yes/no). Thereafter, participants will directly proceed to the baseline assessment via telephone (≈30 min).

##### Post-randomisation: assessment at post-treatment and follow-up

Research team members will collect data via telephone (≈30 min) at post-treatment (12 weeks), and follow-up (6 months post-treatment). We will book a time for assessments via SMS or telephone following the same procedure as for the inclusion interview and baseline assessment.

##### Data recording and entry

Data collected via telephone will initially be recorded on paper forms and subsequently entered independently into Microsoft Excel by two research team members in accordance with standard operating procedures. Entries will be compared and any discrepancies will be identified and resolved.

### Procedures to promote participant retention

We will provide participants who complete the post-treatment (12 weeks) and follow-up (6 months post-treatment) assessments with a gift voucher (100 SEK, approximately €9) after each assessment.

### Outcome data collected for participants who withdraw from trial and/or intervention

All participants will be invited to complete post-treatment (12 weeks) and follow-up (6 months post-treatment) assessments according to the intention-to-treat principle. Participants who withdraw from the intervention but remain in the trial will continue to complete all planned assessments. Participants who withdraw from the trial will not be contacted for further assessments, data collected up to the point of withdrawal will be retained and included in analyses where appropriate.

### Data management

Research data (data) includes: personal data (ie, code list, consent forms, contact details, and data from the Swedish Childhood Cancer Registry and Swedish Tax Agency’s Population Registry); and pseudonymised data (ie, inclusion interviews, assessments at baseline, post-treatment (12 weeks), and follow-up (6 months post-treatment).

A data management plan using DMPonline will be prepared and all data will be processed in accordance with Swedish legislation and the EU General Data Protection Regulation (GDPR, EU 2016/679). We have conducted a data security assessment and information classification in accordance with the Swedish Civil Contingencies Agency guidelines and the principles of Confidentiality, Integrity, and Availability (CIA).

We will store data in fireproof cabinets at Uppsala University and/or in the secure storage solution Allvis, a web-based platform provided by Uppsala University for storing research data.

#### Personal data

We will store the code list (Excel file) linking the unique ID number and personal identification number of each participant in a storage area in Allvis protected by encryption with VeraCrypt, and the code list will be stored separately from other personal and pseudonymised data. All pseudonymised data can be traced back to participants via the code list with unique ID numbers and personal identification numbers.

We will store signed consent forms (paper based), which include participants’ names, personal identification numbers and telephone numbers, in a locked fireproof cabinet at Uppsala University, and signed consent forms will be stored separately from other personal and pseudonymised data.

We will store contact details (Excel file), which includes participants’ personal identification numbers, names, addresses and telephone numbers, in a storage area in Allvis, and contact details will be stored separately from other personal and pseudonymised data.

We will store data from the Swedish Childhood Cancer Registry (Excel file) on a password protected encrypted USB stick in a locked fireproof cabinet at Uppsala University, and data from the Swedish Childhood Cancer Registry will be stored separately from other personal and pseudonymised data.

We will store data from the Swedish Tax Agency’s Population Registry (Excel file) in a storage area in Allvis protected by encryption with VeraCrypt, and data from the Swedish Tax Agency’s Population Registry will be stored separately from other personal and pseudonymised data.

#### Pseudonymised data

We will store pseudonymised data from inclusion interviews, assessments at baseline, post-treatment (12 weeks) and follow-up (6 months post-treatment) (paper based and Excel files) together in a locked fireproof cabinet at Uppsala University and in a storage area in Allvis and, pseudonymised data will be stored separately from personal data.

We will follow Uppsala University guidelines regarding management, storage and archiving of data. We will store passwords for USBs and VeraCrypt passwords securely using a password manager. Only the principal investigator and authorised research team members have access to the code list and password manager.

We will store all data, including the code list, for a period of 10 years after the date of the last publication. At this date, a decision will be made by the principal investigator to either continue to store or destroy the data. If there is no longer a need to identify participants, for example, for data verification purposes, the code list will be destroyed. As the destruction of data is carried out at least 10 years after the date of the last publication, it is not possible to specify in advance exactly how data will be destroyed, however, this will take place in accordance with Uppsala University guidelines on data management, storage and archiving of data at that time.

### Statistical methods

Quantitative data analysis is primarily descriptive and addresses outcomes related to procedural, intervention, and methodological uncertainties. Research team members will conduct the analysis following a pre-specified statistical analysis plan, with PAB members contributing to sense-making and interpretation of results. We will illustrate trial flow using a CONSORT diagram for pilot and feasibility studies.^51^

We will use independent samples t-test (continuous data) and χ² test (categorical data) to examine potential differences in sociodemographic characteristics between those invited versus those who consent.

We will calculate the proportion of those invited who consent, are assessed for inclusion, are included and are randomised, alongside 95% CIs. We will calculate the proportion of participants in the intervention and control group who complete questionnaires at baseline, post-treatment (12 weeks), and follow-up (6 months post-treatment), alongside 95% CIs. We will calculate the proportion of responses missing in each questionnaire for the intervention and control group at baseline, post-treatment (12 weeks), and follow-up (6 months post-treatment), alongside 95% CIs. We will calculate the proportion of the intervention group who complete the minimum treatment dose, alongside 95% CIs.

For clinical, health economic and process outcomes, we will report means and standard deviations (SDs) for normally distributed continuous variables, medians and interquartile ranges (IQRs) for non-normally distributed continuous variables, and frequency and percentages for categorical variables.

We will calculate the SD around the mean score on mental well-being (QWB) for the intervention and control group at post-treatment (12 weeks) and follow-up (6 months post-treatment) to assess variance in mental well-being. We will calculate correlation (Spearman’s ρ) between baseline QWB scores and scores at post-treatment (12 weeks) and follow-up (6 months post-treatment). We will estimate differences in mental well-being between the intervention and control groups by calculating mean changes in the QWB from baseline to post-treatment (12 weeks) and from baseline to follow-up (6 months post-treatment), alongside 95% CIs.

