### The ENGAGE feasibility trial

Research from the intervention development phase informed the feasibility phase (figure 1) where we conducted the single-arm feasibility trial ENGAGE^30^ to examine procedural, intervention, and methodological uncertainties around the internet-administered version of EJDeR and planned trial procedures for a future evaluation of EJDeR in a superiority randomised controlled trial (RCT). Progression criteria were set a priori, following a GO-AMEND-STOP progression framework.^31^ We enrolled 75 participants (56 identified via the Swedish Childhood Cancer Registry and Swedish Tax Agency’s Population Registry, and a further 19 via other recruitment strategies), of which 72 completed baseline assessments and gained access to EJDeR.

Five progression criteria met GO: (1) 11.0% (56/509) were enrolled of the total potential participant population invited via the Swedish Childhood Cancer Registry and Swedish Tax Agency’s Population Registry, criteria ≥9.0%; (2) 24% (18/75) dropped out of the trial and 23.6% (17/72) dropped out of the intervention, criteria ≤30.0%; (3) 0.01–3.9% of questionnaire items were missing, criteria ≤10.0%; (4) 98.7% (74/75), 84.4% (54/64) and 81.4% (48/59) completed telephone interviews at baseline, post-treatment (12 weeks), and follow-up (6 months post-treatment), respectively, of those remaining in the study at each time point, criteria ≥70.0%; and (5) no substantial negative consequences were reported. Two criteria met AMEND: (1) 65.6% (42/64) and 67.8% (40/59) completed online assessments at post-treatment (12 weeks) and follow-up (6 months post-treatment) respectively of those remaining in the study at each time-point, criterion ≥70.0%); and (2) 47.9% (34/71) completed the minimum treatment dose completion, criterion ≥50.0%.

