#### Procedural uncertainties

1. Is there a difference in sociodemographic characteristics between those invited versus those who consent?

2. What proportion of those invited consent, are assessed for inclusion, are included, and are randomised?

3. What proportion of the intervention and control groups complete questionnaires at baseline, post-treatment (12 weeks), and follow-up (6 months post-treatment)?

4. What proportion of responses are missing in each questionnaire for the intervention and control group at baseline, post-treatment (12 weeks), and follow-up (6 months post-treatment)?

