### Sample size

We will recruit 60 participants (30 to the intervention group, 30 to the control group), consistent with the median sample size per arm reported for pilot trials.^74^ With 30 participants per group, we can estimate proportions, for example, completion rates, with reasonable precision: 9.0% randomisation rate (approximately 60/667 invited; 95% CI 7.0% to 11.4%), 70.0% completion of all questionnaires at baseline, post-treatment (12 weeks), and follow-up (6 months post-treatment) (42/60; 95% CI 57.4% to 80.2%), and completion of the minimum treatment dose in at least 65% of participants in the intervention group (20/30; 95% CI 46.0% to 83.6%). These estimates will provide adequate information to inform progression decisions.

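### Consenters are compared with an invited group that includes them, so the planned t-test and χ² test give miscalibrated, conservative p-values (minor)

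*Protocol article*

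**What the plan says.** Research question 1 of the protocol article (Objectives, Procedural uncertainties) asks: "Is there a difference in sociodemographic characteristics between those invited versus those who consent". The Statistical methods section fixes the tests: "We will use independent samples t-test (continuous data) and χ² test (categorical data". It repeats the same pair of groups in giving their purpose: "to examine potential differences in sociodemographic characteristics between those invited versus those who consent".

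Two other statements show how the groups relate:

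- The next paragraph of Statistical methods treats consenters as a fraction of the invited: "We will calculate the proportion of those invited who consent, are assessed for inclusion, are included and are randomised, alongside 95% CIs".
- The section Identification and invitation describes the route to consent, which is the form and envelope posted in the invitation pack: "Those who wish to participate provide consent by returning the consent form in the freepost return envelope".

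The article nowhere limits the comparator to parents who did not consent, and it names no method for nested groups.

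**The concern.** Both tests require two groups with no member in common. Here every consenter also sits in the invited group. At the planned figures, a χ² table built as written would hold 667 + 60 = 727 entries for 667 people.

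This has two consequences. The standard error in the test is not that of the difference being tested, so the p-value is wrong. The difference shown is also smaller than the one between parents who consented and parents who did not.

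With planned uptake of about one in eleven invited parents, who takes part matters for planning the later superiority trial. An overlapping comparison makes a borderline imbalance somewhat easier to miss.

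**Working it through.** **Inputs from the article**

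- Invited N = 667 and randomised n = 60, from Sample size: "9.0% randomisation rate (approximately 60/667 invited; 95% CI 7.0% to 11.4" (per cent). Consenters number at least as many as those randomised. The article gives no figure for consenters.
- For a range, the earlier feasibility trial: "11.0% (56/509) were enrolled of the total potential participant population invited".

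**Assumptions, not in the article**

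- A two-sided 5% level; none is stated for this comparison.
- A true difference of 0.4 SD between consenters and non-consenters, with a common SD.
- 80 consenters as a second case.

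**Reproducing the planned share.** 60/667 = 9.0%. The Agresti–Coull 95% CI is 7.0% to 11.4%, as stated.

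**Algebra.** Let p = n/N and work in SD units.

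1. Difference shown: mean(consenters) − mean(all invited) = (1 − p) × [mean(consenters) − mean(non-consenters)].
2. Standard error used by the planned test: √(1/n + 1/N).
3. True standard error of that difference: √(1/n − 1/N).
4. Ratio of true to assumed: r = √((1 − p)/(1 + p)).
5. True size of a nominal 5% test: 2 × [1 − Φ(1.96/r)].
6. Power of the planned test at difference d: Φ{[(1 − p)d − 1.96 √(1/n + 1/N)] / √(1/n − 1/N)}. The opposite tail is negligible.
7. Power of consenters versus non-consenters: Φ{d/√(1/n + 1/(N − n)) − 1.96}.

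**60 consenters of 667**

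- p = 0.090, so the difference shown is 91.0% of the consenter versus non-consenter difference.
- r = √(0.910/1.090) = 0.914. Size = 2 × [1 − Φ(2.145)] = 3.2%.
- Planned test at d = 0.4: (0.364 − 1.96 × 0.1348)/0.1232 = 0.81, power 79%.
- Disjoint groups (60 versus 607): 0.4/0.1353 − 1.96 = 1.00, power 84%.

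**80 consenters of 667**

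- p = 0.120, so the difference shown is 88.0% of the consenter versus non-consenter difference.
- r = 0.886. Size = 2.7%.
- Planned test at d = 0.4: (0.352 − 1.96 × 0.1183)/0.1049 = 1.15, power 87%.
- Disjoint groups (80 versus 587): 0.4/0.1192 − 1.96 = 1.40, power 92%.

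**At the earlier trial's share (56 of 509, p = 0.110):** the difference shown is 89.0%, r = 0.895 and size 2.9%.

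**Simulation check** (20,000 runs, N = 667, n = 60). With no true difference, the overlapping t-test and the uncorrected χ² test each rejected in 3.3% of runs. With disjoint groups they rejected in 5.2% and 5.0%.

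**What this does to one result.** Suppose a characteristic is present in 38/60 consenters and 303/607 non-consenters. The disjoint χ² test gives p = 0.047. The same data set out as 38/60 against 341/667 invited give p = 0.070.

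**The case against.** **All invited parents are a legitimate comparator.** Setting a sample beside its target population is a fair way to describe representativeness, and for that contrast the point estimate is not biased. This stands: the 9–12% shrinkage is a shortfall only against the consenter versus non-consenter difference. It does not rescue the test, because the standard error is wrong under either reading. With the correct standard error, √(1/n − 1/N) = (1 − p)√(1/n + 1/(N − n)), the factor (1 − p) cancels and the test equals the disjoint one. Naming disjoint groups therefore loses nothing.

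**The wording may be shorthand.** Calling the test independent-samples suggests two separate groups, and the analysis plan, which is not shown, may define them. That is possible. But the same pair of groups appears in both the research question and the analysis text. An analysis plan that follows them literally inherits the error.

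**Little depends on it.** Question 1 has no criterion in Table 2, plays no part in the sample size and does not enter any comparison between arms. The article describes its analysis as mainly descriptive. The section on deciding about progression does take account of outcomes without criteria, but as one input to a judgement made with the steering committee. This stands, and it sets the severity.

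**A stronger reading.** A reader might infer that the check on selection is worthless, or that the trial would wrongly declare selective uptake absent. The documents support neither. The test errs on the conservative side and creates no excess false positives. No significance threshold or decision rule is attached to the comparison. Nor can question 1 be called the only check on who takes part, since the process evaluation has a separate protocol that is not shown.

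**Conclusion.** This is a minor point, but the plan is wrong as written. The stated groups overlap, the stated tests assume they do not, and the p-values are conservative whichever contrast was intended.

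At 60 to 80 consenters of about 667 invited, a nominal 5% test has a true size of about 3.2% to 2.7% and loses about 5 percentage points of power at 0.4 SD. Only borderline results would change. These figures rest on the assumed 5% level, the assumed 0.4 SD and, for the upper case, the assumed 80 consenters. The direction of the error needs none of them, because r is below 1 whenever some but not all invited parents consent.

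The data are unaffected, and so are the progression criteria and the treatment comparison.

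**What to change.** Reword research question 1 and the matching sentence in Statistical methods so that parents who consent are compared with invited parents who do not. Carry the same definition into the analysis plan.

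Restrict the comparison to variables the registries hold for both groups. The section on pre-enrolment registry data lists parents' country of birth. It also lists the child's diagnostic group, age at diagnosis and treatment dates. These are medical rather than sociodemographic, so question 1 should say so if they are to be included. Parent age and sex are not listed there as separate fields and should not be assumed available.

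Report each difference with its 95% CI, which suits a descriptive feasibility question better than a p-value alone.

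The cost is two sentences of rewording. No new data are needed, and the design does not change.

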#### Methodological uncertainties

In ENGAGE, we did not specify a primary clinical outcome measure(s) for a future superiority RCT, nor did we measure mental well-being. We will measure mental well-being as a proposed primary clinical outcome for a future superiority RCT, but sensitivity to change in the population is unknown. The variance and estimated between-group differences in follow-up scores for mental well-being and correlation with baseline scores are unknown. We will require this information to inform a sample size calculation for a future superiority RCT.^50^

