#### Methodological uncertainties

6. What is the variance in mental well-being for the intervention and control group at post-treatment (12 weeks) and follow-up (6 months post-treatment), and is there a correlation with mental well-being at baseline?

7. Is there a difference in mental well-being between the intervention and control group at post-treatment (12 weeks) and follow-up (6 months post-treatment)?

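### The QWB between-group difference is estimated from unadjusted mean changes, which is unbiased but less precise than adjusting the same data for baseline QWB

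*Protocol article*

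**What the plan says.** The rationale (Methodological uncertainties) explains why QWB is measured: "The variance and estimated between-group differences in follow-up scores for mental well-being and correlation with baseline scores are unknown". It continues: "We will require this information to inform a sample size calculation for a future superiority RCT". Question 7 of the objectives then asks: "Is there a difference in mental well-being between the intervention and control group at post-treatment", and the same at follow-up.

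Statistical methods answers with three quantities:

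- the spread: "We will calculate the SD around the mean score on mental well-being (QWB) for the intervention and control group" at both later time points;
- the correlation: "We will calculate correlation (Spearman’s ρ) between baseline QWB scores and scores at post-treatment" and follow-up;
- the difference: "We will estimate differences in mental well-being between the intervention and control groups by calculating mean changes in the QWB from baseline to post-treatment" and from baseline to follow-up, with 95% CIs.

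No baseline covariate is mentioned. Table 3 and the section on randomisation show that baseline QWB is collected before allocation. The same section of the article describes the analysis as mainly descriptive, and Blinding says the trial is not meant for inference about group differences.

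**The concern.** The difference, the SD and the baseline correlation of QWB are the methodological output that the article wants for planning the next trial. With at most 30 participants per arm, each estimate will be imprecise, so the choice of estimator matters more than in a large trial.

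A change score subtracts the whole baseline value, which fixes the regression slope on baseline at 1. If the true slope is smaller, as it is whenever the SDs are equal and r is below 1, the subtraction adds baseline noise. ANCOVA estimates the slope from the data and avoids this. The baseline scores are already there, so the extra width of the interval buys nothing.

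**Working it through.** **Inputs.** Planned size is 30 per arm (Sample size). The 70% completion level in the same section is 42/60, or about 21 per arm. The article gives no SD, correlation, target difference or precision for QWB, so there is no stated figure to reproduce. Results are in SD units, with r as an assumption shown over a range and equal SDs at both times.

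**Variance per participant.**

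- Follow-up score alone: SD²
- Change score: 2·SD²·(1 − r)
- ANCOVA: SD²·(1 − r²)

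The excess of change over ANCOVA is SD²·[2(1 − r) − (1 − r²)] = SD²·(1 − r)², which is zero only at r = 1. The ratio ANCOVA/change is (1 + r)/2, so the standard error of the change-score difference is √(2/(1 + r)) times that of ANCOVA. Change beats the plain follow-up contrast only if 2(1 − r) < 1, that is, r above 0.5.

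**Half-widths at r = 0.5 (1.96 × SE).**

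- 30 per arm, change: 1.96·√(4·0.5/30) = 0.506; ANCOVA: 1.96·√(2·0.75/30) = 0.438
- 21 per arm, change: 1.96·√(4·0.5/21) = 0.605; ANCOVA: 1.96·√(2·0.75/21) = 0.524

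**Over a range of r**, with t quantiles and an allowance for estimating the slope:

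| r | SE ratio, change/ANCOVA | 30 per arm: change / ANCOVA | 21 per arm: change / ANCOVA |
|---|---|---|---|
| 0.4 | 1.195 | 0.566 / 0.478 | 0.683 / 0.580 |
| 0.5 | 1.155 | 0.517 / 0.452 | 0.624 / 0.548 |
| 0.7 | 1.085 | 0.400 / 0.373 | 0.483 / 0.452 |
| 0.8 | 1.054 | 0.327 / 0.313 | 0.394 / 0.379 |

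Ignoring baseline gives 0.517 and 0.624 at every r. The SE ratios are large-sample values; estimating the slope costs about 1/56 = 1.8% of the ANCOVA variance at 30 per arm, which would cancel the gain only for r above about 0.96.

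**Simulation check** (20,000 trials, 30 per arm; standard errors for ANCOVA / change / follow-up only): 0.238 / 0.284 / 0.256 at r = 0.4; 0.211 / 0.233 / 0.261 at 0.6; 0.156 / 0.163 / 0.256 at 0.8. These agree with the formulas.

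**Spearman against Pearson.** The factor 1 − r² in a baseline-adjusted sample size takes Pearson's r. Under bivariate normality Spearman's coefficient is (6/π)·arcsin(r/2): 0.385 at r = 0.4, 0.582 at 0.6, 0.786 at 0.8. For an illustrative next trial (assumed difference 0.3 SD, two-sided 5%, 90% power), putting Spearman's value into 1 − r² moves the number per arm from 197 to 199, 150 to 155 and 85 to 90, an increase of about 1% to 6%. On a simulated skewed 0–72 score the two coefficients agreed within about 0.003. By comparison, with n = 60 and r = 0.6 the 95% CI for r is 0.41 to 0.74. Across that interval 1 − r² runs from 0.83 to 0.45.

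**The case against.** The strongest reply is that this is a descriptive pilot. No criterion in Table 2 uses QWB, and Blinding disclaims inference about group differences. The gain shrinks as r rises, and the article reports high test-retest reliability for the QWB, so r may lie where the standard error loss is only 5% to 8%. An analysis plan that is not shown may also add an adjusted estimate. The first two points stand and keep the matter small. But the rationale calls the correlation unknown, so r below 0.5 cannot be ruled out, and the article does commit to an estimator with 95% CIs.

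Several stronger readings are tempting, and the article does not support them:

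- A reader might infer that mean changes answer a different question from the difference in follow-up scores. Under randomisation the change, follow-up and ANCOVA contrasts have the same expected value. They differ in precision only.
- A reader might take mean changes with CIs as within-arm summaries. The sentence says the differences are between the groups. It is loose only about where the interval attaches.
- A reader might call Spearman's rho a serious error. The gap is at most about 0.02 under normality, errs towards a slightly larger trial and is far below sampling error. A rank correlation is also a reasonable description of a bounded score.
- A reader might infer that the next trial will be sized on the pilot's observed difference. The rationale says only that the information will inform the calculation; it sets no such rule.

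**Conclusion.** The point holds as one of efficiency. The article fixes an unadjusted change-score contrast where a baseline-adjusted one from the same participants would be more precise: the standard error is about 5% to 20% larger for r from 0.8 to 0.4, and for r below 0.5 the planned contrast is worse than not using baseline at all. These figures assume equal SDs at the two times and a range for r that the article does not supply. With unequal SDs the excess variance is (1 − b)² times the baseline variance, where b is the true slope, so it vanishes only if b = 1.

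The follow-up SD and a baseline correlation are still reported, so the residual variance can be approximated for the next trial, whose analysis model the article does not state. No estimate is biased, and no stated figure or progression criterion changes.

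**What to change.** At each of the two later time points, estimate the between-group difference in QWB by ANCOVA with baseline QWB as covariate, or by one mixed model covering both times, and give it with a 95% CI. Report the residual SD. Mean changes by arm can stay as description, and the text should say that the interval belongs to the between-group difference.

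As a secondary addition, report the within-arm Pearson correlation with its CI beside Spearman's rho, since a baseline-adjusted sample size uses Pearson's r.

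The cost is wording in the analysis plan, and a note to the registry if the team treats it as an amendment. No new data, participants or assessments are needed. Because the assessors are unblinded, the change should be dated before any QWB results are compared between arms.
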